### Health economics

To gauge the feasibility of collecting health economic data, data completeness will be summarised by presenting the number and proportion of complete and missing values at each time point. Efficacy will be measured using the CHU-9D measure of health-related quality of life. Data on iCT-PTSD-YP, contact time and indirect time for the intervention will be collected directly from clinicians and service records. Service use estimates will be combined with standard UK sources for unit costs to estimate total costs. The cost of iCT-PTSD-YP will be directly calculated. These data will allow us to index service use and permit preliminary estimates of the potential cost-effectiveness of iCT-PTSD-YP.

### Qualitative analysis

We will carry out qualitative interviews at the end of each participant’s iCT-PTSD-YP. If participants drop out of treatment early, we will endeavour to interview them. Semi-structured interviews using a topic guide will be carried out by a member of the study team who was not involved in treatment. The views and experiences of patients, parents or carers and trial clinicians will be sought in order to gain a multiperspective view of acceptability. Content analysis will be used to explore both commonalities and variations within and between these respondents. We will interview trial participants in both arms about the acceptability of the research procedures including the assessment measures and their views on randomisation. We will invite all participants to take part in qualitative interviews, until data saturation is reached.

### Data monitoring

Project oversight will be provided by a monthly Project Management Group (PMG) attended by all co-investigators. Trial oversight will be provided by a 6-monthly TSC. The TSC will review the protocol, agree the SAP and safeguard the interests of trial participants. The TSC will provide advice to the chief investigator and sponsor. A separate Data Monitoring Committee (DMC) will not be convened. The TSC will monitor AEs and adverse reactions and will convene an emergency DMC if needed.

### AEs

AEs are defined as any untoward occurrence in a trial participant, including events that are not necessarily caused by or related to trial procedures. Serious AEs are defined as AEs that result in death, are life-threatening, require hospitalisation or prolong existing hospitalisation or result in persistent or significant disability or incapacity. Some AEs are expected in this study, and will be reported to the TSC, for example: self-harm not requiring medical attention, increase in suicidal ideation, worsening of PTSD symptoms (defined as 7-point increase in CRIES-8). Serious AEs will be reported to the Chair of the TSC, the Research Ethics Committee (REC) and the sponsor. AEs will be assessed at each assessment time point. Risk monitoring including AE monitoring will be carried out during clinical contact for those allocated to iCT-PTSD-YP. AEs will be monitored and recorded from randomisation to final follow-up.

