**Methods and analysis:**

This protocol describes a two-arm, parallel-groups, single-blind (outcome assessor), early-stage randomised controlled trial, comparing iCT-PTSD-YP with a waiting list (WL) comparator. N=34 adolescents (12–17 years old), whose primary problem is PTSD after exposure to a single traumatic event, will be recruited from 14 NHS Child and Adolescent Mental Health Services in London and southeast England, from secondary schools and primary care in the same region, or via self-referral from anywhere in the UK using the study website. Individual patient-level randomisation will allocate participants in a 1:1 ratio, randomised using minimisation according to sex and baseline symptom severity. The primary study outcomes are data on feasibility and acceptability, including recruitment, adherence, retention and adverse events (AEs). The primary clinical outcome is PTSD diagnosis 16 weeks post-randomisation. Secondary clinical outcomes include continuous measures of PTSD, anxiety and depression symptoms. Regression analyses will provide preliminary estimates of the effect of iCT-PTSD-YP on PTSD diagnosis, symptoms of PTSD, anxiety and depression relative to WL. Process-outcome evaluation will consider which mechanisms mediate recovery. Qualitative interviews with young people, families and therapists will evaluate acceptability.

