### Outcomes

The schedule for assessments is presented in table 1.

**Table 1 T1:** Study schedule

Measure	Study period					
	Screen 0–1 week	Pre 0 weeks	Weekly (*iCT only*)	Mid 0+6 weeks	Post 0+16 weeks	Follow-up 0+38 weeks (*iCT only*)
Enrolment						
Eligibility screen	x					
Provide study information	*x*					
Gain informed consent		*x*				
Online assessment						
Dawba		*x*				
Interview						
Demographic interview						
CAPS-CA-5		*x*			*x*	
CGAS		*x*			*x*	
*Adolescent questionnaires*						
CPSS-5		*x*			*x*	*x*
CRIES-8		*x*	*x*	*x*	*x*	*x*
RCADS-C		*x*			*x*	*x*
CPTCI		*x*		*x*	*x*	*x*
TMQQ		*x*		*x*	*x*	*x*
Rumination items		*x*		*x*	*x*	*x*
CHU-9D		*x*			*x*	*x*
Adverse events				*x*	*x*	*x*
Carer questionnaires						
SDQ-P		*x*			*x*	*x*
RCADS-P		*x*			*x*	*x*
CA-SUS		*x*			*x*	*x*
Adverse events				*x*	*x*	*x*
Qualitative interviews						
Adolescents					*x*	
Carers					*x*	
Therapists					*x*	

CAPS-CA-5, Clinician Administered PTSD Scale for DSM-5: Child and Adolescent version; CA-SUS, Child and Adolescent Service Use Schedule; CGAS, Children’s Global Assessment Scale; CHU-9D, Child Health Utility Index 9D; CPSS-5, Child PTSD Symptom Scale for DSM-5; CPTCI, Child Post Traumatic Cognitions Inventory; CRIES-8, Children’s Revised Impact of Event Scale, 8-item version; DSM-5, Diagnostic and Statistical Manual of Mental Disorders; iCT, internet-delivered cognitive therapy; PTSD, post-traumatic stress disorder; RCADS-C, Revised Children’s Anxiety and Depression Scale—child version; RCADS-P, RCADS—parent version; SDQ-P, Strength and Difficulties Questionnaire—parent version; TMQQ, Trauma Memory Quality Questionnaire.

The primary outcomes for the study are data on feasibility, adherence and acceptability, which will be reported using the metrics specified below.

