### Participant timeline

All participants will be assessed three times during the study: pre-treatment (week 0), mid-treatment (week 6 post-randomisation) and post-treatment (week 16 post-randomisation). Participants in iCT-PTSD-YP will complete a brief weekly measure of PTSD symptoms (CRIES-8) and mood (Likert scale) on the application, and a follow-up assessment (week 38 post randomisation). The first participant was randomised on 24 August 2020, and the last participant was randomised on 20 October 2021. The trial is currently closed to new recruitment.

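### Adverse events are looked for more often and for longer in iCT-PTSD-YP than on the waiting list, so a by-arm AE summary using all recorded events would be inflated for iCT relative to equal ascertainment

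*Protocol article*

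**What the plan says.** Collection common to both arms: the AEs section says "AEs will be assessed at each assessment time point". Under Participant timeline and Table 1, the post-baseline assessments shared by both arms are weeks 6 and 16, with AE reports from adolescents and carers at each.

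Collection in iCT only:
- The AEs section adds "Risk monitoring including AE monitoring will be carried out during clinical contact for those allocated to iCT-PTSD-YP". The iCT-PTSD-YP section puts therapist contact at once a week or more during therapy, which lasts 12 weeks.
- Participant timeline says "Participants in iCT-PTSD-YP will complete a brief weekly measure of PTSD symptoms (CRIES-8) and mood (Likert scale) on the application". Table 1 confirms that the weekly CRIES-8 column is for iCT only.
- Table 1 has a week-38 follow-up, iCT only, that includes AEs. The AEs section says "AEs will be monitored and recorded from randomisation to final follow-up". The last scheduled WL assessment is week 16.

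One of the listed expected AEs is "worsening of PTSD symptoms (defined as 7-point increase in CRIES-8"). The section does not say whether the rise is counted from baseline or from the preceding score.

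On status, the abstract says "The primary study outcomes are data on feasibility and acceptability, including recruitment, adherence, retention and adverse events (AEs"). The Outcomes section says "The primary outcomes for the study are data on feasibility, adherence and acceptability, which will be reported using the metrics specified below", and neither that sentence nor the metrics after it name AEs.

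**The concern.** The arms differ in how long AEs are observed, how often they are sought and by what means. An event count from such data reflects looking as well as risk. The effect is most direct for the score-based event: a noisy scale compared with a fixed threshold on many occasions crosses it by chance more often than on two occasions.

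The trial is meant to inform a larger one, and with 17 participants per arm a few events found only by closer watching could change the impression of safety. They could suggest that iCT worsens PTSD when it does not, or hide that it reduces worsening.

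**Working it through.** **Inputs from the protocol.** 17 per arm (Sample size); WL last assessed at week 16 and iCT at week 38 (Table 1); 12 weeks of therapy with at least weekly contact (iCT-PTSD-YP); weekly CRIES-8 in iCT only; threshold of 7 points (AEs). The protocol states no AE rate, so there is no AE figure to reproduce.

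**Observation time, as planned and before dropout.**
- iCT: 17 × 38 = 646 person-weeks.
- WL: 17 × 16 = 272 person-weeks.
- Ratio: 646 / 272 = 2.375.

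With the same true rate and full detection in both arms, for instance one event per person per 16 weeks, raw counts would be 17 in WL and 17 × 38/16 = 40 in iCT.

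**Occasions to week 16.** iCT: 12 weekly, one of which falls at week 6, plus week 16, giving about 13. WL: weeks 6 and 16, giving 2. Cutting iCT off at week 16 equalises time (272 versus 272) but leaves 13 versus 2 looks. Using only weeks 6 and 16 in both arms gives 2 versus 2.

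**CRIES-8 worsening with no true change.** Assumptions not in the protocol: independent normal errors with SD σ at baseline and at each look, scores rounded to whole points, every completed score screened, rise counted from baseline. A participant is flagged if any look exceeds baseline by at least 7. Simulation with 400,000 participants per case:

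| σ | WL, 2 looks | iCT, 13 looks | Expected of 17: WL v iCT |
|---|---|---|---|
| 2 | 2% | 9% | 0.4 v 1.5 |
| 3 | 11% | 33% | 1.9 v 5.6 |
| 4 | 21% | 51% | 3.5 v 8.7 |
| 5 | 28% | 62% | 4.8 v 10.6 |

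Without rounding, σ of 3 to 4 gives 9% to 18% in WL and 28% to 47% in iCT. As a hand check, one unrounded look gives 1 − Φ(7/(σ√2)). That is 1 − Φ(1.65) = 5% at σ = 3 and 1 − Φ(1.24) = 11% at σ = 4. Two looks sharing one baseline should give somewhat less than double, as they do.

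**The same with improvement in iCT only.** Assume a linear 8-point fall over 12 weeks in iCT and no change in WL, with rounded scores:

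| σ | WL, 2 looks | iCT, 2 looks | iCT, 13 looks |
|---|---|---|---|
| 3 | 11% | 1% | 10% |
| 4 | 21% | 4% | 25% |

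On equal looks iCT shows clearly less worsening. With the weekly looks added, that advantage almost disappears at σ = 3 and reverses at σ = 4. With a 12-point fall, the 13-look figures are 7% and 18%, against the same 11% and 21% in WL.

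**The case against.** The strongest reply is that the protocol never plans the comparison at issue. The AEs section covers definition, collection and reporting. The regression models under Clinical outcomes cover the clinical endpoints. The feasibility analysis section allows some outcomes to be reported for iCT alone. The SAP, which is not shown, could set a common window. This stands in part: a reader might infer that AE rates by arm are a planned primary comparison, and the text does not support that. Only the abstract puts AEs among the primary outcomes, and it specifies no rate or test. What remains is that the unequal collection is fixed in the protocol itself, and an SAP can undo it only if each AE record shows how and when the event was found.

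A second reply is that between-arm differences are declared exploratory. That answers imprecision; it does not remove a systematic difference in ascertainment.

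A third reply concerns the size, and much of it stands. Weekly AE monitoring is inferred by combining two sections, and Table 1 has no AE mark in its weekly column. Nothing says each weekly score is screened for a 7-point rise. The error SD and the independence of errors are assumed. WL adolescents and carers may report at weeks 6 and 16 on events since the previous visit, so for events such as self-harm more contacts need not bring proportionally more reports. A reader might also infer that iCT must show more AEs than WL; the improvement scenarios show that this is not assured.

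**Conclusion.** The concern holds in a limited form. As written, AE ascertainment differs by arm in duration (38 versus 16 weeks), in frequency (about 13 versus 2 occasions by week 16, if weekly contacts and scores count) and in method. A by-arm summary of all recorded AEs would be inflated for iCT relative to equal ascertainment.

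The person-week ratio of 2.4 follows from the protocol's own figures. The roughly two- to four-fold excess in false CRIES-8 worsening across SDs of 2 to 5 rests on the assumed SD, independent errors, no true change and screening of every score. The size is therefore uncertain, and the result in a given trial could be an apparent excess in iCT or a masked benefit. Closer monitoring during therapy is not itself a fault.

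**What to change.** State in the analysis plan that any between-arm AE summary covers randomisation to week 16 and uses only sources common to both arms: the AE assessments and CRIES-8 at weeks 6 and 16, with change from baseline for this comparison. Tabulate separately, labelled iCT only, AEs found at therapist contacts, through the weekly CRIES-8 or after week 16. Both restrictions are needed, because the week-16 cut-off alone leaves the difference in frequency. Reconcile the abstract and the Outcomes section on whether AEs are a primary outcome. Safety monitoring and reporting stay as they are.

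The cost is a paragraph of wording and a source and date flag on each AE record. The drawback is fewer AEs in the comparative table, although every event is still listed.

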## Ethics and dissemination

### Ethical approval

The study was approved by a UK Health Research Authority (HRA) Research Ethics Committee (REC; 19/LO/1354). The study is sponsored by King’s College London.

### Protocol amendments

We were initially funded to run a three-arm feasibility RCT comparing iCT-PTSD-YP with face-to-face CT-PTSD and WL. The COVID-19 pandemic national lockdown was implemented before we started to recruit to the planned three-arm trial. Restrictions in CAMHS services due to lockdown meant that we could not offer face-to-face CT-PTSD. Therefore, after consultation with the funder and the TSC we changed the design to the current two-arm trial and received HRA and REC approval to proceed. This change was made before recruitment started, and before registration on ISRCTN.

Further protocol amendments will require approval from the REC, and where relevant will be passed on to the trial register.

### Consent and assent

For participants aged under 16, informed consent will be provided by carers and the young person will be asked for their assent. Participants aged 16 years or older can provide informed consent without their parent or caregiver’s involvement. Please see online supplemental file for copies of consent and assent forms.

10.1136/bmjopen-2021-054852.supp2Supplementary data

### Confidentiality

Information with regards to participants will be kept confidential. The treating clinician and research team involved in day-to-day trial management will have access to personally identifiable data so that they can maintain contact with participants throughout the study. Participants will be assigned a study ID. All outcome data will be stored against this study ID so that data are anonymised.

### Access to data

All investigators will have access to the final trial data set. Our intentions are to maximise the availability and sharing of our data for the benefit of the wider research community, while providing for its long-term preservation and making due allowance for the potential commercial value of findings. The PMG will make the decision on whether to supply research data to a potential new researcher. Independent oversight of data access and sharing will be provided by the TSC. Data released to the wider community after publication will be fully anonymised.

### Dissemination policy

There are no publication restrictions and findings will be disseminated broadly to participants, healthcare professionals, the public and other relevant groups. The study findings will be published in peer-reviewed journals. The full trial protocol is available from PS.

## Discussion

PTSD in children and adolescents is a significant public health burden. Highly efficacious treatments exist but are not widely accessible. Remotely delivered iCT-PTSD has potential to facilitate a step change in improving accessibility of an evidence-based therapy for youth. The data gathered in the current trial will inform the design and size of a future scaled up trial to evaluate remotely delivered iCT-PTSD-YP.
